## Abstract

**Background:**

While most Australian children are vaccinated, delays in vaccination can put them at risk from preventable infections. Widespread mobile phone ownership in Australia could allow automated short message service (SMS) reminders to be used as a low-cost strategy to effectively ‘nudge’ parents towards vaccinating their children on time.

**Methods:**

AuTOMATIC is an adaptive randomised trial which aims to both evaluate and optimise the use of SMS reminders for improving the timely vaccination of children at primary care clinics across Australia. The trial will utilise high levels of digital automation to effect, including eligibility assessment, randomisation, delivery of intervention, data extraction and analysis, thereby allowing healthcare-embedded trial delivery. Up to 10,000 parents attending participating primary care clinics will be randomised to one of 12 different active SMS vaccine reminder content and timing arms or usual practice only (no SMS reminder). The primary outcome is vaccine receipt within 28 days of the scheduled date for the index vaccine (the first scheduled vaccine after randomisation). Secondary analyses will assess receipt and timeliness for all vaccine occasions in all children. Regular scheduled analyses will be performed using Bayesian inference and pre-specified trial decision rules, enabling response adaptive randomisation, suspension of any poorly performing arms and early stopping if a single best message is identified.

**Discussion:**

This study will aim to optimise SMS reminders for childhood vaccination in primary care clinics, directly comparing alternative message framing and message timing. We anticipate that the trial will be an exemplar in using Bayesian adaptive methodology to assess a readily implementable strategy in a wide population, capable of delivery due to the levels of digital automation. Methods and findings from this study will help to inform strategies for implementing reminders and embedding analytics in primary health care settings.

**Trial registration:**

ANZCTR: ACTRN12618000789268.

**Supplementary Information:**

The online version contains supplementary material available at 10.1186/s13063-023-07097-3.

## Administrative information

Note: the numbers in curly brackets in this protocol refer to SPIRIT checklist item numbers. The order of the items has been modified to group similar items (see http://www.equator-network.org/reporting-guidelines/spirit-2013-statement-defining-standard-protocol-items-for-clinical-trials/).

### Background and rationale {6a}

Vaccination is a highly effective preventative strategy of improving population-level child health [1], but its efficacy is undermined by under-vaccination (not receiving all vaccines for which a person is eligible) and delayed vaccination (not receiving vaccines at the age or time recommended). Reasons for under-vaccination are complex and vary between people; our previous research has shown that practical barriers, such as ease of access to appointments and remembering appointments, may be more important determinants of under-vaccination in Australia than concerns about vaccine safety or doubts about necessity or efficacy [2]. Furthermore, the relative intensity and complexity of the vaccine schedule in early childhood that now covers a wide range of vaccine preventable diseases may present a competing demand to busy families, with some parents simply unaware that a vaccine dose has become due [3, 4].

A low number of small to moderate scale randomised control trials (RCTs) and observational studies have assessed the impact of SMS-based interventions on vaccine uptake and timeliness in childhood vaccination. Most of these studies have assessed impact in specific at-risk populations including lower socioeconomic service areas. Evidence from these studies suggests that SMS reminders can induce small to moderate improvements in vaccination rates and timeliness compared to no SMS (alternative reminders) [5–10] and no reminders [9–11]. Some studies reported greater improvements in vaccine coverage when the reminder included embedded educational messages [6, 8, 10, 12].

The COVID-19 pandemic has highlighted the importance of consistent public health messaging strategies for promoting vaccination. Whether the effectiveness of SMS reminders is influenced by (1) their timing of delivery in relation to the due date or (2) can be improved by framing messages to target potential health benefits, the risks of disease or the social motivators for vaccination, requires evaluation among a large representative population. SMS reminders for routine childhood vaccination have also not been evaluated in an Australian context, leading to uncertainty on how and when to implement this intervention effectively in primary care. Adaptive trial methods and automation of clinical trial processes may provide opportunity to enable these large-scale evaluations in primary care.

## Aim

We aim to evaluate and optimise the use of personalised, provider-initiated SMS reminders for improving the timeliness of routine vaccination among Australian children.

### Objectives {7} and outcomes {12}

#### Primary objective

The primary objective is to determine whether, compared to usual practice, a personalised SMS reminder with specific timing and message framing, will improve the rate of timely vaccination in primary care, that is, the proportion of children vaccinated within 28 days of the scheduled date for a routine childhood vaccine dose.

A child and their siblings may receive more than one scheduled vaccination during the follow-up period; the parent will be the unit of randomisation and will only be randomised once. The parent whose behaviour we seek to change can only be considered naïve to the intervention on the first child-vaccination occasion; therefore, the primary analysis will be performed on the outcome of the first child-vaccination occasion for each parent after randomisation (the *index vaccine occasion* and the *index child*).

#### Primary outcome

The primary outcome is receipt of the index vaccine within 28 days of the vaccine scheduled date for the index child.

#### Secondary objectives

The secondary objectives are to determine whether, compared to usual care, a personalised parental SMS reminder with specific timing and content framing, will improve timely vaccination (vaccination within 28 days of the scheduled date) and reduce the time to vaccination from the scheduled date, for all age-scheduled vaccines after randomisation for all children (index child and siblings).

#### Secondary outcomes

The secondary outcomes are as follows:The time elapsed from 14 days before the due date to administration of the index vaccine, censored at 42 days after the due date;Vaccination status at 28 days post scheduled vaccine due date (binary variable; vaccinated vs not vaccinated) for all children and all vaccine doses;The time elapsed from 14 days before the due date to administration of any vaccine dose, censored at 42 days after the due date for all children and all vaccination doses.

#### Trial design {8}

This is a pragmatic multi-arm Bayesian adaptive randomised superiority trial that will be enrolling a non-fixed sample size of no fewer than 1500 and no more than 10,000 parents at participating primary care clinics. The design (see Fig. 1) has 13 arms, including 12 active and one usual care arm (no SMS reminder). We will repeatedly measure the time in days from 14 days prior to the vaccine due date to vaccine administration over the childhood vaccine schedule for each child under the care of the enrolled parent, until the administration of each child’s last scheduled vaccine dose at 4 years old, or until the study ends.

**Fig. 1 Fig1:**
[figure not shown]
Trial design of the AuTOMATIC study. SMS reminders will comprise different framing options including neutral reminders (indicating vaccine due date), positive (benefit of vaccination), risk-based (risks of disease) and social (responsibility to other children). A full description of the intervention is below in the “Intervention description {11a}” section

The trial will use several adaptive features including adaptive sample size, response adaptive randomisation and arm dropping for inferiority. The allocation of participants to the usual care arm will be fixed at 20% of all randomisations or 0% if discontinued for inferior effectiveness at a subsequent scheduled analysis. Initial randomisation ratios will be equal across the 12 active arms with scheduled analyses using a Bayesian response adaptive algorithm.

The AuTOMATIC trial will perform regular scheduled automated analyses, starting when 1500 parents have reached the primary endpoint, and then after every 500 further parents have reached 28 days after the scheduled date of the index vaccine dose. These analyses will estimate for each arm the posterior probability that it is the best performing arm (highest proportion of index vaccines received by day 28), which will be used to update the future allocation ratios to favour assignment to the better performing arm/s. Enrolment will continue until the maximum sample size is reached or until a pre-specified stopping rule is met. A final analysis will be undertaken at the end of the study to determine secondary objectives.

## Methods: participants, interventions and outcomes

### Study setting {9}

Parents will be enrolled from primary care (general practice, GP) and public vaccination clinics participating in SmartVax across Australia. SmartVax is an Australian software platform installed at GP clinics primarily for active surveillance of adverse events following immunisation (AEFI). The platform interrogates the practice clinical record databases (e.g. Best Practice™ or Medical Director™) and has SMS functionality for issuing surveys to capture self-reported AEFI and vaccine reminders. Clinics across a range of geographical locations will be invited to participate to try to ensure broad sociodemographic representation, including from regional (remote) locations.

### Eligibility criteria {10}

#### Inclusion criteria

To be enrolled, a participant must (1) be a parent of at least one child who is 2 weeks—4 years old and who is registered with a SmartVax-associated clinic or a community vaccination clinic, (2) have their mobile phone number and their child’s name and date of birth recorded in the clinic’s information system and (3) have a child who has received at least one vaccine dose at the clinic previously, except for infants < 2 months old who are yet to receive a first scheduled vaccine dose. This is to target parents who are known to have used the clinic service for childhood vaccination and minimises parents who may be registered at the clinic for medical check-ups but choose to vaccinate their child elsewhere (i.e. community clinics). The system will also check to ensure there is a minimum 4-week window between the last vaccine dose administered and the current vaccine due-date to avoid sending SMS reminders that may confuse parents on catchup schedules.

#### Exclusion criteria

The parent will be excluded if any of the following apply: (1) the parent(s) has requested not to be contacted by the clinic via SMS; (2) the parent(s), in the opinion of clinic staff, would be unsuitable for inclusion in the study, for example because they are known to attend for routine vaccinations elsewhere or because they are conscientious objectors to vaccination; (3) the critical information required to produce the unique study identifier is incorrectly recorded in the clinic’s information system (i.e. parent mobile phone number, child’s date of birth, child’s first and surname); and (4) parents of twin and multiple births will not be eligible as it is not possible to produce a unique child identifier for them in the system.

#### Who will take informed consent {26a}

A waiver of consent has been approved for this study by the University of Western Australia Human Research Ethics Committee (Ref: 2019/RA/4/1/8810) on the basis that the risk to participants is low and that disclosing the study’s objectives is likely to undermine its integrity through selective participation and effects on participant behaviour.

Many patients already receive SMS from clinics, so issuing SMS for vaccine reminders is not considered overly intrusive or burdensome. The study team will have no direct contact with participants and only de-identified data will be extracted and analysed in accordance with the *Australian Privacy Act 1988* [13], the National Statement on the Ethical Conduct of Human Research [14] and other legal and regulatory requirements.

Although participants will not be prospectively informed of their participation in the clinical trial, they can opt-out of receiving further SMS reminders at any stage. Participants who opt out will have their de-identified data included and analysed up to the time of opt-out, but future vaccine occasions will not be captured electronically by SmartVax.

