### Interventions

#### Explanation for the choice of comparators {6b}

Usual care (control arm) is no SMS vaccine reminder but might include other non-SMS reminders like telephone or written reminders. Most parents receive a letter from the Australian Government’s universal healthcare payer, Medicare, including a notice if childcare subsidy payments are at risk due to missed vaccinations. Parents in the usual care arm will not receive an SMS reminder for upcoming vaccination, but they may receive an appointment confirmation reminder via SMS if they have already scheduled an appointment where such confirmations are used routinely by the clinic.

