### Data collection and management

#### Plans for assessment and collection of outcomes {18a}

Whenever a child attends a participating clinic for vaccination, the vaccine type and vaccination date and time will be entered in the electronic practice information system and will be transferred automatically to the study REDCap database. Data on participants will continue to be captured until the trial is complete, the child receives their 4-year-old scheduled vaccine doses or the parent opts out of receiving further SMS reminders.

The data captured will include the unique practice identifier; unique parent study identifier; unique child study identifier, parent postcode, child date of birth, current scheduled vaccine (age in months) and due date, assigned study arm, scheduled date of issuing the SMS reminder, SMS sent date, SMS delivery success, most recent prior vaccination date at the clinic, type of vaccine administered and opt out of future SMS.

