#### Methods in analysis to handle protocol non-adherence and any statistical methods to handle missing data {20c}

Where digital errors may occur, for example, a clinic server malfunction leading to no SMS being sent as assigned, participants will be included in each scheduled analyses according to their intended assignment. As this is equally likely to occur in any of the active arms, there is no significant risk of bias. The data capture system is designed to ensure all fields are populated so missing data is not expected; however, in the event any data is missing, we will not use imputation in our analyses.

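### Opting out of SMS reminders also ends outcome capture, so later outcomes are lost mostly in the active arms, and the fate of an open index outcome is unsettled

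*Protocol article*

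**What the plan says.** Under 'Who will take informed consent {26a}', parents are not told of the trial, but "they can opt-out of receiving further SMS reminders at any stage". The same paragraph sets the consequence for data: "Participants who opt out will have their de-identified data included and analysed up to the time of opt-out". For anything that falls due afterwards, the sentence ends with a second limit: "but future vaccine occasions will not be captured electronically by SmartVax". 'Plans for assessment and collection of outcomes {18a}' lists the events that end capture besides completion of the trial: "the child receives their 4-year-old scheduled vaccine doses or the parent opts out of receiving further SMS reminders".

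On the comparator, 'Explanation for the choice of comparators {6b}' says "Parents in the usual care arm will not receive an SMS reminder for upcoming vaccination", although "they may receive an appointment confirmation reminder via SMS if they have already scheduled an appointment".

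On missing data, section {20c} says the system fills all fields, "so missing data is not expected; however, in the event any data is missing, we will not use imputation in our analyses".

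'Interim analyses {21b}' brings into each analysis every index occasion whose due date lies 28 days or more in the past, and makes no exception for opt-outs. 'Adverse event reporting and harms {22}' has opt-out counts reviewed, with the independent committee told if an active arm has many.

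**The concern.** Declining a message and withdrawing from outcome measurement are different acts, and the protocol merges them. Opt-out happens after randomisation and is plausibly prompted by the reminder, so the loss depends on the assigned arm. It is plausibly also related to willingness to vaccinate. Under 'Intervention description {11a}', a child already recorded as vaccinated triggers no message. A reminder-prompted opt-out before the outcome can therefore come only from families still unvaccinated at the send time. That group differs between the day −14, day 0 and day +7 arms, so comparisons among active arms are exposed as well as comparisons with usual care.

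If such families are left out, an active arm looks better than it is whenever opt-outs vaccinate less often than others. If an empty record is read as not vaccinated, the arm looks worse. Should this reach the primary outcome, it would enter the posterior probabilities behind allocation, arm dropping and stopping. At 10,000 parents the superiority threshold in {21b} is 0.95 − 0.25 = 0.70, so modest distortion could affect which arm ranks first.

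Section {20c} does not deal with this. Its argument that bias is unlikely concerns digital failures spread evenly over the active arms, not opt-outs.

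**Working it through.** **What is lost, by outcome**

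- *Later doses and siblings.* {26a} and {18a} agree that these are not captured after opt-out. Two of the three secondary outcomes cover all children and doses, so loss there follows from the rule itself.
- *Index occasion open at opt-out.* {26a} gives up future occasions, and an occasion already under way is not clearly one of those. {18a} ends capture at opt-out without exception. {21b} includes every index occasion once 28 days have passed. Together these permit three treatments: followed to day 28, excluded, or recorded as unvaccinated.
- *Index time to vaccination.* This outcome runs to day 42, so the same ambiguity applies for longer.

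**The plan's own figures.** The article gives no opt-out rate or attrition allowance, so there is no figure on this point to reproduce. The nearest reference is a power of about 0.87 for an odds ratio of 1.4 ('Sample size {14}'). It comes from simulations in a supplement that is not shown and cannot be reproduced strictly. A simplified simulation (600 trials, independent arms, flat priors, the thresholds of {21b}) gave 0.91, which is the same order. The concern does not depend on this figure.

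**Inputs for the size of the bias**

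- p = 0.80, the expected 28-day vaccination rate in {20a}. Its intercept prior mean of 1.37 corresponds to 79.7%.
- True odds ratio 1.00, and no loss in usual care.
- d = share of an active arm lost before the index outcome: 1%, 2% or 5%. **Assumed.**
- q = proportion of opt-outs who in fact vaccinate by day 28: 0.4 to 0.8. **Assumed.**

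**Formulas**

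- Excluded: observed rate = (p − d·q)/(1 − d)
- Counted as unvaccinated: observed rate = p − d·q
- Apparent odds ratio = observed odds ÷ 4, since 0.80/0.20 = 4

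Extremes at d = 5%: excluded with q = 0.4 gives (0.80 − 0.02)/0.95 = 0.8211, odds ratio 1.15. Counted as unvaccinated with q = 0.8 gives 0.80 − 0.04 = 0.76, odds ratio 0.79.

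| d | Excluded | Counted as unvaccinated |
|---|---|---|
| 1% | 1.00–1.03 | 0.95–0.98 |
| 2% | 1.00–1.05 | 0.91–0.95 |
| 5% | 1.00–1.15 | 0.79–0.89 |

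**Day +7 arms.** Let v be the share vaccinated by day 7 (assumed 50–70%), so only 1 − v are messaged. With 1–5% of those opting out, the arm loses (1 − v)·d, or 0.3% to 2.5%. The vaccination rate of opt-outs is taken as (0.80 − v)/(1 − v), or half that. At v = 0.5 and d = 5% the loss is 2.5%. Excluded with q = 0.3 gives 0.7925/0.975 = 0.8128, odds ratio 1.09. Counted as unvaccinated with q = 0.6 gives 0.785, odds ratio 0.91. Over the whole range the odds ratio is 1.01–1.09 or 0.91–1.00.

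**Accumulation over occasions.** If a constant share d opted out at each reminded occasion (assumed), the share already lost before a fourth occasion would be 1 − (1 − d)³: 3.0% at d = 1%, 5.9% at 2% and 14.3% at 5%.

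**The case against.** The best defence has five parts.

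1. *Loss is not confined to the active arms.* Usual-care parents may get appointment confirmations by SMS, the platform also sends adverse-event surveys ('Study setting {9}'), and the recorded field in {18a} is an opt-out from future SMS generally. Parents who had already refused SMS contact are excluded before randomisation. This stands. A reader might infer that only the active arms lose outcomes; the documents support only that they lose most of them.
2. *The primary outcome may be untouched.* If {21b} governs and the open index occasion is followed, there is no bias in the primary analysis, the allocation weights or the stopping rules. This stands as a possible reading. {18a} points the other way, so the text does not settle it.
3. *The size is assumed, and its direction depends on a coding rule not shown.* This stands. At 1–2% loss the shift is small beside the odds ratio of 1.4.
4. *A rule exists and monitoring is in place.* {20c} does say that nothing is imputed, and {22} provides for committee notification and possibly removal of an arm. Detailed coding may sit in the analysis plan, and its absence from the article is not a fault. But neither provision recovers an outcome, and the expectation of no missing data remains at odds with the opt-out rule.
5. *Ending capture may be deliberate.* Under a waiver of consent, opt-out is the only participant exit described, so retaining data afterwards is for the ethics committee to decide. This stands and shapes the fix.

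**Conclusion.** The point holds in limited form, as a should-fix. The protocol makes an opt-out from messages end outcome capture, and it says elsewhere that missing data are not expected. Loss is certain for any later dose or sibling occasion after an opt-out, and will fall mostly in the active arms, possibly unevenly by framing and timing. Whether the primary outcome is affected is unresolved, because {26a}, {18a} and {21b} have not been reconciled.

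If it is affected, the null odds ratio could appear as high as about 1.05 or as low as 0.91 at 1–2% loss, and as high as 1.15 or as low as 0.79 at 5%. These limits rest on an 80% base rate from the protocol, on assumed opt-out rates, on assumed vaccination of 40–80% among opt-outs, and on no loss in usual care.

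A reader might go further and conclude that allocation and stopping are already being distorted. The documents do not show that: it would need both the less favourable reading of the index rule and an opt-out rate that is nowhere given.

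**What to change.** 1. State in {26a}, {18a} and {21b}, in matching words, that the index occasion is followed to day 28 whatever the SMS opt-out status, and to day 42 for the index time outcome.
2. Subject to ethics committee agreement, make an SMS opt-out stop messages only. Continue the passive, de-identified extraction of vaccination dates and analyse all parents as randomised on every occasion. 'Data management {19}' has outcomes drawn from clinic records, and usual-care parents are captured without any reminder, so capture does not depend on messaging.
3. If the committee does not agree, keep opt-outs in every denominator, report opt-outs by arm including usual care, and give each contrast twice: with all opt-outs counted as vaccinated, and with all counted as unvaccinated.
4. Replace the statement in {20c} that missing data are not expected with one that names opt-out as a source and refers to the handling above.

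The cost is an ethics amendment, a change to the extraction rule and some wording; the fallback costs only extra analysis. The downside of step 2 is that data are kept on parents who declined messages, which the committee would have to accept. If capture continued after opt-out, this source of bias would disappear.
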